**Location of Clinical Trial**

Pôle d’Endocrinologie, Centre de Recherche en Nutrition Humaine Ile de France ([name]) INSERM U872 (Eq.7), Pitié-Salpêtrière, [name]

Overview

| Visits | V1  Inclusion | V2  **J0-Reg-HC** | V3  **J7-Reg-HC** | V4  J42-**RHC**  **J0 - RST** | V5  **J84 –RST** |
| --- | --- | --- | --- | --- | --- |
| Days | -14 à -1 | 0 | 7±1 | 42±4 | 84±10 |
| Inclusion/exclusion criteria | X | X |  |  |  |
| Study intervention |  | x | x | x | x |
| Signed informed consent |  | x |  |  |  |
| TA |  | x |  |  | x |
| Weight (height) |  | x | x |  | x |
| Electrical impedance |  | x |  | x | x |
| Waist circumference |  |  | x | x | x |
| **Phenotype and nutritional assessment**  - Anthropometric measurements including body composition (DEXA)  - Nutrition diary | x | x    x  x | x  x | x  x  x | x  x  x |
| **Metabolic assessment**  - Glycemia  - Insulinemia  - Glucose tolerace test  - Cholesterol, LDL-, HDL- Cholesterol, TG | x  x | x  x  x |  | x  x  x | x  x  x |
| **Inflammation assessment**  - CRP  - SAA  - IL6  -TNF |  | x  x  x  x |  | x  x  x  x | x  x  x  x |
| **Adipokine assessment**  - Leptin  - Adiponectin |  | x  x |  | x  x | x  x |
| **Serum bank ( 7 ml)** |  |  |  | x | x |
| Subcutaneous adipose tissue needle biopsy |  | x | x | x | x |
| **Fecal assessment** |  | x |  | x | x |

RHC : Hypocaloric diet

RST : Weight stabilization diet

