## Procedures for obtaining subject consent

Written informed consent of all people who participate in biomedical research must be obtained by the investigator, registered in the order of medical doctors, declared as an investigator with the sponsor before any act can be performed under the research protocol and whatever the act, in accordance with the Public Health Code, Article L1122-1.

Information will be given orally and in writing in the first part of the form of information and consent (Annex 2). The form will be signed at the bottom of each page so that the person suitable for the research confirms receipt of this information. The information is written in plain language understandable to the person. It must contain all the elements that the person must be informed about, in accordance with the Public Health Code, Article L. 1122-1.

The consent of the subject participation in research is collected in writing on the second part of the information and consent form. This second part should be written in clear, understandable language for the person undergoing the research. It must contain all the elements that the person consents. Consent is given by affixing the signature and inscription, from the hand of the person who is willing to take part in the research, first name, last name and date of consent.

In addition, the investigator collects dates and sign the consent form in the position reserved for him and ensures 1) that the form is accurate and no information or date is missing, 2) that an original copy of the document is given to the patient. The investigator maintains a second copy in a safe place and to which access is controlled and 3) a third original copy is placed in a secure location for the attention of the sponsor. The third copy shall not be opened by the sponsor, but retained with the permanent records of the study.

The investigator must ensure that the person is suitable for the research will have time to make a decision freely and be able to read and understand the information form and consent.

The information form and consent is a document that has been approved prior to the implementation of research by the CPP, on the occasion of the review of the protocol.

The participation of people in this protocol shall be registered on the national register of persons undergoing biomedical research, managed by the Ministry of Health.

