### Description of the participating subjects:

Inclusion Criteria

1 . BMI 27-38 kg/m2
2 . Subjects aged from 25 to 65 years. Postmenopausal for at least 6 months.
3 . Subject has given his consent to participate by writing
4 . Non-diabetic subjects
5 . Fasting blood glucose less than 1.26 g / l

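### The visit table schedules signed consent at V2, after V1 assessments have begun, against the protocol's own rule that consent precedes any act

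*Protocol*

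**What the plan says.** The overview visit table at the front of the protocol sets the visit days as "Days | -14 à -1 | 0 | 7±1 | 42±4 | 84±10", so V1 (labelled inclusion) falls before V2 (day 0). Three of its rows put something at V1:

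- eligibility: "Inclusion/exclusion criteria | X | X", that is, at V1 and again at V2;
- phenotype and nutritional assessment: "Nutrition diary | x | x x x | x x", with one mark at V1;
- metabolic assessment: "Cholesterol, LDL-, HDL- Cholesterol, TG | x x | x x x", with two marks at V1 against four listed items (glycemia, insulinemia, glucose tolerance test, lipids).

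The consent row reads "Signed informed consent | | x": blank at V1, marked at V2 and nowhere else.

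Under Protection of persons, the section on obtaining subject consent requires the investigator to have written consent "before any act can be performed under the research protocol and whatever the act". The inclusion criteria list "Subject has given his consent to participate by writing" and "Fasting blood glucose less than 1.26 g / l".

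**The concern.** The consent rule is absolute and the table does not follow it. The visit table is the page that staff are likely to work from when they plan and run a visit, and the protocol does not say which place prevails when the table and the text disagree. Staff who follow the table would start protocol assessments before the participant has signed.

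What is at stake is participant protection, not the analysis. The protocol describes the study as offering no direct individual benefit, so valid consent is the main basis for performing any procedure. People who fail screening are the most exposed: if they are turned away at V1 they never reach the only visit at which the table has them sign.

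**Working it through.** No sample size, power or error rate is involved. The check sets the V1 and V2 columns of the table beside the text.

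**1. What the table places before consent.** V1 has one eligibility mark, one phenotype/nutritional mark and two metabolic marks: 1 + 1 + 2 = 4 marks, of which 3 are assessments. It has 0 consent marks. The only consent mark is at V2.

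**2. The gap.** V2 is day 0 and V1 is day -14 to -1. The longest gap is 0 - (-14) = 14 days and the shortest is 0 - (-1) = 1 day. No permitted V1 date falls on the day of consent.

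**3. Whether the rule leaves room for this.** The consent section covers any act under the protocol. It has no carve-out for screening, and no other section supplies one. V1 is a numbered visit in the study schedule, so its assessments are acts under the protocol.

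**4. Whether V1 could be routine care.** The sections on serious adverse events and on independent monitoring speak of ordinary occupational medicine visits. However, the recruitment section says that subjects come through public advertising. Someone who answers an advertisement and attends a numbered study visit is not there for usual care.

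**5. What the V1 metabolic marks mean.** The row has two marks for four items at V1, and three marks for the same four items at V2, V4 and V5. Marks and items do not pair one to one, so the table does not identify the two V1 items. All four items are blood measurements. Glycemia is the most likely, because a fasting glucose limit is an eligibility criterion. The exclusion criteria also need transaminases, renal clearance and haemoglobin, and the table has no row for any of these.

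**6. What the sampling section says.** The section on collection of human biological samples gives blood sampling at days 0, 7, 42 and 84. The day -14 to -1 window is not in that list. The protocol is therefore also inconsistent on whether blood is drawn at V1.

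**7. What is not scheduled before consent.** The adipose tissue biopsy, inflammatory markers, adipokines and faecal assessment are first marked at V2, the visit at which consent is marked.

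**8. Whether the blank cell is an artefact of text extraction.** The consent row has the same number of cells as the header, and the rows around it line up. The point also rests on a mark that is present at V2, not only on one that is absent at V1.

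**The case against.** The strongest reply is that the consent section already states the rule in full. On that view the table is a one-page overview with a misplaced mark, and a site that reads the protocol text will obtain consent first. This stands in part. It means that the contradiction does not show what happened to any participant. It does not remove the contradiction, because the table gives an explicit and different visit.

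Four stronger readings are tempting, and the document does not support them:

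- *Every subject is subjected to a breach.* This would follow only if sites acted on the table against the consent section. The protocol does not show that they would.
- *Insulin is measured before consent.* Taking the first two items in order gives glycemia and insulinemia, but step 5 shows that the marks cannot be assigned that way. Even a V1 blood draw is not certain, given the sampling days in the collection section.
- *The inclusion criterion on written consent cannot be met.* Eligibility is marked at both V1 and V2, so this criterion can be completed at V2. The conflict is with the consent section, not with the inclusion criteria.
- *V1 data would be unusable.* No passage says so, and no endpoint is defined on a V1 value. The objectives compare status before and after the diet, gene-expression kinetics start at day 0, and the metabolic and eligibility rows are marked again at V2.

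It is also fair to say that the consent form is an annex not included in this copy and may state when it is signed. If it does, the table still needs to agree with it.

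**Conclusion.** The point holds as an internal contradiction on participant protection. The visit table puts signed consent at V2, while V1 already has the eligibility check and three assessment marks; the consent section requires written consent before any act. On the table's timing, protocol assessments come 1 to 14 days before consent, and people screened out at V1 never sign.

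The conclusion rests on reading the V1 marks as acts under the protocol, which the numbered visit and the recruitment route support. It does not depend on which two metabolic items are meant. Even if no blood is drawn at V1, the eligibility check and the phenotype/nutritional assessment still precede consent.

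The effect is conditional on a site following the table. The point bears on no sample size, endpoint or analysis, and it does not show that any participant was in fact assessed without consent. It should nevertheless be corrected before the schedule is used, because the study offers participants no direct benefit and the correction is trivial.

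**What to change.** 1. In the visit table, move the signed-consent mark from V2 to V1 and note that it comes before any V1 procedure. At V2, confirm only that consent still stands.
2. State when the written information is given, so that the person has time to decide before signing at V1, as the consent section requires.
3. State which metabolic items are done at V1, and reconcile those marks with the sampling days in the section on collection of human biological samples. If blood is drawn at V1 for eligibility, the sampling section should list it; if not, the V1 marks should be removed and the source of the eligibility glucose stated.

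The cost is a correction to one table and a sentence or two of text. The form is signed at a visit that already takes place, and no visit, test or analysis is added. Because the change concerns participant protection, the sponsor should judge whether it must be notified to the ethics committee under the protocol's amendment section.

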# Justification of test 1 – requirements

This is a clinical protocol in the framework of the **Programme de l’Agence Nationale de l’Alimentation (ANR) 2007-2010 (**French National Food Agency (ANR)) with INRA: MICROBIAL GENOMICS LARGE SCALE - GMGE; coordinator: [name]. The project is selected in the framework of a Franco-Chinese agreement between the ANR and the Ministry of Science and Technology of China (MOST). It will be in association with a Chinese project.

**1. 1 – CONTEXT AND STATE OF THE ART**

**Obesity and nutrition transition.**

The nutrition transition observed over several decades in Western countries and more recently emerging (such as China) has been accompanied by an obesity epidemic and increased metabolic (insulin resistance, dyslipidemia) and cardiovascular complications. According to figures from WHO (www.who.int), about one billion adults are overweight (BMI> 25kg / m²), of which 300 million are obese (BMI> 30kg / m²). In France, the prevalence of obesity is now 12.4% (against 8.2% in 1997) in the population over 15 years. Severe obesity is rarely associated with a genetic cause (1) (2).

Complex interactions between susceptible genes and environmental factors are the most common causes of obesity. Among these factors, the nutritional transition contributes significantly to alterations in the regulation of the functioning of adipose tissue (increased release of fatty acids, secretion of adipokines ...) and its relationship with other tissues critical for weight control (liver, muscle, pancreas and brain). Obesity is now recognized as a state of chronic low grade inflammation, characterized by the increase of systemic inflammatory markers. These markers exert, in addition an pro or anti-inflammatory, immune and metabolic functions that are related in part to the accumulation of adipose tissue in the circulating macrophages, with hyperplasia and hypertrophy of the adipocytes (3-5) (6, 7)

Even though some but not all environmental factors have been defined, the epidemic of obesity appears virtually impossible to control for the time being, and the mechanisms associated with fat mass expansion need to be urgently identified (Hill et al 2003).

Recently studies in rats and humans suggested a potential role of the human intestinal microbiota in energy harvest from food. This new paradigm opens perspectives for recommendations and dietary adaptations that may contribute in tackling this major problem of public health.

**Human intestinal microbiota**.

The human intestinal microbiota has many functions, most of which are beneficial to the host. In turn, homeostasis of the intricate interactions between food, microbiota and host is essential to the maintenance of health and well being ; and conversely, the disruption of any constituent is susceptible to lead to perturbations and digestive pathologies (functional, inflammatory or infectious..). The importance of the intestinal microbiota and the production of lipopolysaccharide (LPS) in the inflammatory diseases and metabolic syndrome has been demonstrated in rodents (8-10).

The relationship between changes in the intestinal bacterial flora, the inflammatory status and adipose tissue has not yet been explored in humans. Emerging chronic diseases and could be related to alterations in the composition of the microbiota (dysbiosis).

**Microbiota and weight gain.** In 1983, Wostmann et al observed that germ-free rodents required 30% more calories than conventional animals to maintain body-mass. Mechanisms allowing to explain this observation remained elusive until recent studies of the group of Jeffrey I. Gordon that suggest a role of the intestinal microbiota in energy harvest from food [Bäckhed et al., 2005, Sonnenburg et al., 2005] and in regulation of fat storage mechanisms [Bäckhed, 2004]. It was shown that 8 weeks old germ-free mice eat more, exercise less but have a lesser volume of fat tissues than their conventional (normally colonized) counterparts. Within two weeks, ex germ-free mice associated with a microbiota had a 20% increase in body-fat (DEXA measurements) and emerging insulin-resistance in spite of a 30% decrease

in food intake [Backhed, 2004]. No change in gene expression for Acetyl-CoA carboxylase, FAS, aP2 or PPAR-gamma were observed but the activity of lipoprotein lipase was increased. Comparison of ex germ-free mice associated with the microbiota of lean *versus* obese (ob/ob) mice showed that the transfer of the “obese” microbiota induced a more efficient energy harvest from the diet [Turnbaugh et al 2006.Nature]. This was correlated with a dysbiosis in the obese mice faecal microbiota characterized by an increased representation of the phylum Firmicutes and a reduced representation of the phylum Bacteroidetes [Ley et al., 2005].

These results from animal studies were completed by two independent human studies. Comparison of the microbiota composition between lean and obese humans and its evolution in obese patients loosing weight during a low calories or low fat intervention indicated a lesser proportion of Bacteroidetes and increased Firmicutes in obese subjects that tended to revert to that of lean controls upon low calory dietary intervention [Ley et al 2006]. Dynamics of microbiota composition and bacterial fermentation products in obese patients upon low calory intervention showed a reduced concentration of butyrate and lesser proportions of the *Roseburia*-*Eubacterium rectale* subgroup (Phylum Firmicutes) and

*Bifidobacterium* genus as obese patients were losing weight [Duncan et al 2007]..

**Bacterial**

**colonization**

**LPL activity**

**in adipocytes**

**storage of triglycerides**

**in liver and adipocytes**

**hepatic**

**lipogenesis**

**fiaf gene**

**in**

**epithelium**

**oxydation**

**of fatty acids**

**degradation of**

**dietary**

**polysaccharides**

In man as in rodents, the composition of the microbiota seems to determine the efficacy of energy harvest from food, by mechanisms that could influence weight gain or weight loss. Germ-free animals are protected against diet-induced obesity and the impact of the microbiota on the efficacy of calory harvest from the diet has been associated in part with the regulation of specific host genes at the level of intestinal epithelial cells. Target eukaryote signalling molecules modulated by the microbiota in mice included Resistin-like molecule Beta (RelmB) and Fasting induced adipose factor (Fiaf), both increased upon conventionalization (He Gastroenterology 2003 ; Backhed PNAS 2007). RelmB acts as a proinflammatory immuno-cytokine but also as a hormone involved in body-weight control (Sholima

Diabetologia 2005). Fiaf 1) acts as an inhibitor of lipoprotein lipase, thereby increasing storage of triglycerides in adipocytes and 2) increases fatty acid oxidation by reduction of Cpt1, Mcad, Pgc1alpha gene expression (Backhed PNAS 2007). In turn, Fiaf-KO mice lose protection against fat storing activity and gain weight.

The gut microbiota is an essential environmental factor that regulates fat storage. Nevertheless, the signalling molecules of bacterial origin have yet to be identified

**Human intestinal metagenomics**.

Metagenomics is a relatively new and powerful approach to study the genomes of all microbes in an ecological niche. The genomic content of our resident intestinal microbial community is largely unknown due to the inability to culture the vast majority of its dominant microbes. In metagenomics, the microbial population is extracted from its environment, the DNA is purified, and, using high throughput shotgun cloning techniques, the entire sample is sequenced. From such data, the repertoire of genes of both cultured and yet uncultured microbes can potentially be deduced. This permits the design of generic tools for massive microbiomic profiling of the intestinal ecosystem. In addition, large metagenomic inserts can be subjected to a functional investigation, giving access to yet totally unexplored biological resources. Beyond its innovative character, the usefulness of metagenomics has already been well documented (Reisenfeld, 2004 ; *The new science of metagenomics : revealing the secrets of our microbial planet*, National Research Council of the National Academies, The National Academies Press, Washington DC. 2007).

Initial developments applying metagenomics to the human intestinal microbiota have been limited to sequence-based exploration of the biodiversity of the microbial communities (Manichanh et al 2006, Eckburg et al 2006) or the gene repertoire of only two individuals (Gill et al 2006). The functional metagenomics strategy has so far been limited to soil (Williamson et al AEM 2005) and animal intestinal environments (Walter et al AEM 2005; Beloqui et al JBC 2006). We have only just begun to apply it to the human intestinal ecosystem (Gloux et al, 2007).

**1.2 – *Project aims AND INNOVATIVE ASPECTS***

**Project objectives: scientific and socio-economic**

The global obesity epidemic imposes a huge and rapidly growing challenge for public health services. The **overall aim of MICRO-Obes** is to investigate the possibility of a significant relationship between nutritional and metabolic status on the one hand, and the gut microbiota on the other hand, thereby opening novel avenues to understand, prevent or reverse this condition. To reach this overall aim, **MICRO-Obes** has the following objectives:

- Scientific and technological objectives :
- Sequence the dominant gene repertoire of the human intestinal tract and identify sequence signatures of health/obesity
- Develop high-throughput methodologies for metagenomics profiling
- Define the impact of nutritional transition on the intestinal microbiota and identify metagenomics signatures of nutritional transition
- Identify functions involved in host-microbe interactions with relevance to obesity
- Socio-economic objectives :
- Diagnostics : Develop tools to analyze metagenomic data. The novel strategies proposed for the analysis of the human intestinal microbiota in health and diseases combine several advantages: they are high throughput, near exhaustive by the depth of exploration that will determine the sensitivity of the method, and they combine assessment of composition with that of the genetic makeup and hence functional potentials of the ecosystem.
- Nutritional recommendations: Provide strategic information for the adaptation of nutritional recommendations to patients based on intestinal microbiome characteristics. This will be made possible by the identification of microbial signatures of obesity and nutritional transition and by exploration of the functional meaning of the observed Dysbiosis.
- Functional foods: Provide knowledge-based recommendations for novel strategies to prevent obesity. The knowledge of deviations associated with disease will be most valuable to define strategies aiming at restoring a microbiota as close as possible to that of healthy individuals.

**1.3 - Originality/novelty within the project**

The project is based on the application of the metagenomics approach, both in its sequence-based and function-based developments. The metagenomics approach will allows to clone, sequence and describe the functional gene core - c.a. the repertoire of genes - of the intestinal microbiota of healthy individuals and obese patients, irrespective of the culturability of the source-microorganisms, which is essential since over 80% of dominant human intestinal bacteria have no cultured representative to date.

The project will devote a significant effort to contribute to the development of novel procedures and standards for storing, comparing and annotating metagenomics data. In that respect, the project will be strongly coupled to corresponding efforts in China, and will benefit from a worldwide concerted effort which is monitored by INRA following a consensus workshop held in Paris in October 2005 (Human Intestinal Metagenomics Initiative – Paris Recommendations). The first large set of metagenomics sequence data was released in 2006 (Gill et al 2006) and consisted of 140 000 reads allowing to detect 50 000 genes. The sequencing effort of the present project is far greater with over 2 million reads tentatively leading to identify over 700 000 genes, a sizable fraction of the expected 3 million genes on the basis of 1000 dominant species per human intestinal microbiota.

**The protocol presented below relates to the clinical protocol conducted in France in obese subjects:** Quantification of the relationship between nutritional status, inflammatory and metabolic on one part, and the intestinal microbiota on the other part.
The impact of the nutrition transition on the intestinal microbiota and identification of metagenomic signatures of the nutrition transition will be carried out by other partners of INRA and the group Genoscope in EVRY. Biological samples will be thus collected for further analysis. These include urine and blood samples and preparation of fecal water for carrying out metabolomic analysis and the stools for analysis of proteome of the microbiota (metaproteomics) analyzes. Methodologies are available within the partnership.

